## Abstract

**Background:**

Up to 18% of adolescents will engage in an act of self-harm before young adulthood, with the majority of acts occurring in private. Mobile apps may offer a way of providing support for young people at times of distress to prevent self-harm.

**Objective:**

This is a proof-of-concept study designed to explore the safety, acceptability, feasibility, and usability of a smartphone app, BlueIce, with young people who are self-harming.

**Methods:**

In this phase I open trial we will evaluate BlueIce, a smartphone app developed and coproduced with young people with lived experience of self-harm. BlueIce includes a mood-monitoring diary, selection of mood-lifting techniques based on cognitive behavior therapy and dialectical behavior therapy, and direct access to emergency telephone numbers. We will recruit young people (n=50) attending specialist child and adolescent mental health services with a current or past history of self-harm to trial BlueIce as an adjunct to their usual care. Questionnaires and interviews will be completed at baseline, postfamiliarization (2 weeks), and at follow-up (12 weeks after baseline) to assess safety, app use, and acceptability. Interviews will be undertaken with clinicians to assess the feasibility of BlueIce within a clinical setting.

**Results:**

Recruitment occurred between May and November 2016. The recruitment target was 50, and by the beginning of November 54 young people had been referred.

**Conclusions:**

This study is the first to evaluate an app specifically developed with young people for young people (under the age of 18 years) who self-harm. It will determine whether BlueIce is acceptable, how often it is used, and whether it is safe and does not have any unintentional adverse effects. This information will determine whether a feasibility trial to test recruitment, randomization, retention, and appropriate outcome measures should be pursued.

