## Methods

### Study Design

This is a phase I open trial where eligible young people will be invited by their mental health clinician to use BlueIce. The study was funded by the Health Foundation (2143 Oxford Health National Health Service [NHS] Foundation Trust), and the protocol was approved by the NHS South West—Exeter Research Ethics Committee (reference 16/SW/0018).

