### Sample Size

This is an initial feasibility study and as such no formal power calculation was undertaken. For this phase I safety trial we plan to recruit 50 young people, a sample that will be sufficient to reach saturation through analysis of data collected in semistructured interviews [22].

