### Statistical Analysis

We will describe the cohort in terms of age, gender, and previous self-harm and report recruitment, completion, and drop-out rates. Safety will be assessed by the percentage of participants who report problems, a worsening of mood, or an increase in self-harm. Mean and standard deviations of ratings (potential harm and help) will be reported.

Acceptability will be determined by satisfaction ratings and through analysis of semistructured interviews. Interviews will be audiorecorded and transcribed. They will then be analyzed using a predefined framework derived from the interview schedule and adapted and revised on the basis of participant responses [23]. The interviews will also assess usability and how often young people used the app and which features.

Feasibility will be assessed by examining referral flows by teams and professional groups. We will also interview referring clinicians to obtain their views about usability, usefulness, and fit with clinical practice.

Outcome data from standardized questionnaires and reported changes in self-harm will be treated as preliminary and will not be subject to extensive analysis. We will conduct an exploratory analysis using descriptive statistics, where appropriate, to report pre- and post-use changes.

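### The abstract says the study will determine whether BlueIce is safe and without adverse effects; one uncontrolled group of 50, sized for interview saturation, can only estimate harm rates imprecisely

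*Protocol article*

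**What the plan says.** The article describes the safety question in two strengths.

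**The stronger wording.** The abstract's Conclusions say the study will determine "whether it is safe and does not have any unintentional adverse effects", and that this information will decide whether a feasibility trial follows. The Discussion names the focus on evaluation and on establishing safety as a further strength of the design. Sample Size uses the label of a safety trial: "For this phase I safety trial we plan to recruit 50 young people".

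**The softer wording.** The abstract's Objective, Aims of the Study and the opening of the Discussion speak only of exploring safety, and the Objective calls the study proof of concept. Sample Size also states: "This is an initial feasibility study and as such no formal power calculation was undertaken".

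**The design.** Study Design: "This is a phase I open trial where eligible young people will be invited by their mental health clinician to use BlueIce". There is no control group. The number 50 is justified as "a sample that will be sufficient to reach saturation through analysis of data collected in semistructured interviews". Statistical Analysis says: "Safety will be assessed by the percentage of participants who report problems, a worsening of mood, or an increase in self-harm". The Safety section adds semistructured interviews after familiarization and at follow-up, and participants' ratings of how far the app might make them self-harm or might help. Means and standard deviations of these ratings are to be reported.

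The Discussion names two limitations: reliance on clinicians to recruit, and retrospective self-report of self-harm. It mentions neither the precision of the sample nor the lack of a comparator.

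**The concern.** Saturation concerns whether further interviews would bring new themes. It says nothing about how rare a harm the sample could detect, or how high a rate it could rule out. A conclusion about safety and the absence of adverse effects needs that second property, and nothing in the sample size rationale supplies it.

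There is also a problem of attribution. Under Setting and Participants, those enrolled have self-harmed in the past 4 weeks or expect to do so again, and all receive ongoing face-to-face care. Some will worsen and some will improve whatever the app does. The article gives no background rate for this population and plans no comparison group to provide one.

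At stake is how the result will be read. The population is 12 to 18 years old, and the abstract ties the decision on the next trial to this information. If few or no problems are seen, the present wording invites the statement that the app has no adverse effects, when the data would still be compatible with a rate that matters.

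**Working it through.** **Inputs from the article.** Planned sample 50, single group (Sample Size, Study Design). Safety measure: percentage with problems, worse mood or more self-harm (Statistical Analysis). No alpha, power, target rate or dropout rate is given, so there is no statistical calculation of the plan's own to reproduce.

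**Assumption.** Participants may stop at 2 weeks (Study Procedure), so the evaluable number may fall below 50. I show 40 and 30 as assumed values; the article gives neither.

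**Step 1: what zero events would exclude.** With 0 of n affected, the exact (Clopper-Pearson) two-sided 95% upper limit is 1 − 0.025^(1/n).

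| Evaluable n | Calculation | Upper limit |
|---|---|---|
| 50 (planned) | 1 − 0.025^(1/50) | 7.1% |
| 40 (assumed) | 1 − 0.025^(1/40) | 8.8% |
| 30 (assumed) | 1 − 0.025^(1/30) | 11.6% |

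The one-sided 95% limits, with 0.05 in place of 0.025, are 5.8%, 7.2% and 9.5%.

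**Step 2: how easily a harm is missed.** The chance of seeing no event at a true rate p is (1 − p)^n. For n = 50:

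- p = 1%: 1 − 0.395 = 0.605, about 60%
- p = 2%: 0.98^50 = 0.364, about 36%
- p = 5%: 1 − 0.923 = 0.077, about 8%

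At p = 2% the chance rises to 0.98^40 = 45% and 0.98^30 = 55% (0.446 and 0.545) with the assumed 40 and 30 evaluable.

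**Step 3: precision when events do occur.** The safety measure is broad, so a non-zero count is the likelier case. Exact two-sided 95% results for n = 50:

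- 1 of 50 (2%): upper limit 10.6%
- 2 of 50 (4%): upper limit 13.7%
- 5 of 50 (10%): 3.3% to 21.8%
- 10 of 50 (20%): 10.0% to 33.7%

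**Step 4: what these intervals describe.** Each is an interval for how often the event happens among app users who are also in treatment. None is an interval for how often the app causes it. That would need the rate without the app, which the article neither gives nor plans to measure.

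**Step 5: scale.** With no events, a two-sided upper limit of 5% needs 72 participants, 2% needs 183 and 1% needs 368. This is not an argument for a larger study; it shows how far 50 is from supporting a statement that adverse effects are absent.

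**The case against.** Much of the case on the other side stands.

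- **The study is openly exploratory.** The aim is worded that way in several places, a power calculation is disclaimed, and Statistical Analysis treats questionnaire results and changes in self-harm as preliminary. True, but this shows that the concluding claim goes further than the aim. The caveat about preliminary results does not reach the safety conclusion.
- **Safety does not rest on a percentage alone.** Interviews at two time points and ratings of potential harm and help give participants' own views on attribution. That is useful, but a participant's view of cause does not replace a comparator.
- **Zero events is unlikely.** The measure takes in problems of any kind, and the Safety section counts crashes and freezes. This is right: the zero-event limits are a best case, and reporting must cover any count.
- **The decision concerns a feasibility trial, not general release.** This limits the consequence and is a reason for proportion. A randomized study could supply the missing comparator.
- **Intervals may stand in an analysis plan that is not shown.** So their absence here is not itself a fault. The mismatch between the claim and the basis of the sample size remains whatever that plan says.

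Three stronger readings are tempting, and the article does not support them. A reader might infer that it promises to find the app safe; the text says whether, so no result is presupposed. A reader might infer that 50 participants leave rates up to 12% open; with 0 of 50, rates above 7.1% are excluded at the two-sided 95% level, and 11.6% needs an assumed 30 evaluable. A reader might infer that referrals are passed off as recruitment, since "by the beginning of November 54 young people had been referred" is set beside a target of 50; the figure is plainly labelled as referrals, and Statistical Analysis commits to reporting recruitment, completion and drop-out.

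**Conclusion.** The point holds as a mismatch between a stated conclusion and the design. No calculation in the article is wrong, and a study of 50 is not too small for an exploratory aim. The study can estimate, with wide intervals, how often problems, worse mood and more self-harm occur among users. It cannot settle whether adverse effects are absent.

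In the most favourable case, 0 of 50, rates up to 7.1% remain open, and a 2% harm would be missed altogether about one time in three (36%). These figures assume that all 50 are evaluable, that events are fully reported and that participants are independent. Fewer evaluable participants or under-reporting, which the Discussion itself raises for self-report, would weaken the evidence further. The attribution problem does not depend on any of these figures: without a comparator it remains at any sample size.

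**What to change.** 1. **Abstract, Conclusions.** Replace the claim by wording such as: the study will give a preliminary estimate of how often problems, worsening of mood and increased self-harm occur among young people using BlueIce; without a comparison group, such changes cannot be attributed to the app or ruled out as its effect. This matches the exploratory wording of the Objective and the Aims.
2. **Discussion, strengths.** Describe the focus as a preliminary assessment of safety instead of its determination.
3. **Statistical Analysis.** Report each safety percentage with its actual denominator and an exact two-sided 95% confidence interval, whatever the event count.
4. **Discussion, limitations.** Add the lack of a comparator and the limited precision, for example that even 0 of 50 would leave rates up to 7.1% open.

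The Results section says post-use assessments are still under way, so all of this can be done before the findings are written up. It takes a few sentences and one extra column in a results table; no new data are needed. The downside is a less favourable stated conclusion.

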## Introduction

### Overview

Self-harm is defined as intentional self-poisoning or self-injury, irrespective of type of motive or the extent of suicidal intent [1]. Self-harm is a risk factor for suicide. Although suicide rates in those under the age of 18 years are comparatively low, approximately half of those who commit suicide have been found to have a previous history of self-harm [2]. However, the majority of self-harm in adolescence is self-destructive and often occurs without suicidal intent (nonsuicidal self-injury).

While suicide rates in this age group are low, self-harm is unfortunately common with community studies from many countries consistently reporting a lifetime risk of 13% to 18% [3-7]. Of those who self-harm, half will report multiple self-harming events [6]. For example, in a UK community survey of young people aged 12 to 16 years from 8 schools, 15% reported acts of self-harm over the past 12 months with 55% reporting self-harm over 2 consecutive 6-month episodes [8].

In community surveys in developed countries, self-cutting is the most commonly reported method of self-harm whereas self-poisoning is more common in those who present at accident and emergency departments [5,6,9]. However, comparatively few episodes of self-harm result in hospital presentations with most being undertaken in private and remaining hidden [10].

Although suicide is comparatively uncommon in adolescents, it is the second or third leading cause of death within this age group [10]. Self-harm is associated with an increased risk of mortality and suicide. A 10-year follow-up study in the United Kingdom of young people who presented at hospital following an episode of self-harm found that of those who subsequently died, half had committed suicide [11].

In terms of risk factors, self-harm is associated with a range of sociodemographic and educational factors (eg, gender, lower socioeconomic status, sexual orientation), life events (eg, trauma, abuse, family breakdown), and psychological factors (eg, depression, drug and alcohol misuse, impulsivity) [10].

### Interventions for Self-Harm

A UK review by the National Institute of Health and Care Excellence (NICE) recommends that all children under 16 years of age attending hospital following self-harm should be admitted to a pediatric ward and assessed by an experienced mental health practitioner [1]. In terms of interventions, NICE recommends a 3- to 12-session psychological intervention with the aim of reducing self-harm. NICE recommends that it is tailored to individual need and could include cognitive behavioral, psychodynamic, or problem-solving elements [1]. However, comparatively few trials of interventions for children and adolescents who self-harm have been reported. A recent UK Cochrane review concluded that “there is not much evidence on which to draw conclusions on the effects of interventions for self-harm in this population“ [12]. The review found little support for group-based therapy but suggested that therapeutic assessment, mentalization, and dialectical behavior and cognitive behavior therapy warrant further evaluation. Finally, it recommended that any new therapeutic interventions should be developed in collaboration with patients to ensure patients’ needs are met.

### Telemedicine

Telemedicine is the use of information and communication technologies to increase access to care and improve health outcomes [13]. Adolescents are familiar with and frequent users of technology. A survey by the Office of Communications, the regulatory body supervising the communications industry in the United Kingdom, found that nearly all young people aged 12 to 15 years (98%) have Internet access [14]. Approximately 90% of 15-year-olds have a smartphone with ownership increasing with age. Smartphones therefore offer an accessible way of delivering and supporting mental health interventions for this age group.

One particular area that has seen a phenomenal expansion in recent years is the development of smartphone apps. Increasingly these have been developed to help with a range of mental health problems [15]. However their development has significantly outpaced research, and the evidence for their efficacy is largely unknown [15]. In terms of self-harm, no smartphone apps have been specifically developed for young people (under the age of 18) who self-harm.

### BlueIce Development

The development of BlueIce has followed the Medical Research Council framework for the development and evaluation of complex interventions [16]. The original idea was discussed with a group of young people who had a lived experience of self-harm. The young people thought that a smartphone app could improve self-management and provide a helpful way to manage distress and prevent self-harm at times of crisis.

The content of the app was informed by theoretical approaches that appeared promising in treating self-harm—in particular, cognitive behavior therapy (CBT) and dialectical behavior therapy (DBT). The structured nature of these therapies facilitated the incorporation of core therapeutic techniques into a mobile app. BlueIce therefore includes ideas from CBT (behavioral activation, thought challenging, and mood lifting activities) and DBT (mindfulness and distress tolerance).

Further meetings with young people focused on app content, design, and presentation. A beta version of BlueIce was produced which was reviewed by the young people and a group of child mental health professionals. Further recommendations for content and design were suggested and these were incorporated into the second beta version. This was reviewed again with the young people who positively endorsed the app.

BlueIce was developed for Android operating systems and was coded natively. Although it does not connect or interact with existing health care systems, data stored on BlueIce can be reviewed with the young person’s mental health clinician during routine clinical appointments.

### Aims of the Study

The aim of this study is to undertake a phase I trial to explore the safety, acceptability, feasibility, and usability of BlueIce with young people aged 12 to 18 years who are self-harming.

## Methods

### Study Design

This is a phase I open trial where eligible young people will be invited by their mental health clinician to use BlueIce. The study was funded by the Health Foundation (2143 Oxford Health National Health Service [NHS] Foundation Trust), and the protocol was approved by the NHS South West—Exeter Research Ethics Committee (reference 16/SW/0018).

### Setting and Participants

The study will be undertaken in specialist child and adolescent mental health services (CAMHS) provided by Oxford Health NHS Foundation Trust. The Trust serves a wide geographical area that includes Bath and North East Somerset, Buckinghamshire, Oxfordshire, Swindon, and Wiltshire.

Eligible participants will be aged 12 to 18 years with a history of repeated self-harm. Participants may be currently self-harming (within the past 4 weeks) or have a history of self-harm and feel that they will harm themselves again. BlueIce is designed to be used alongside specialist CAMHS so young people must be in receipt of an ongoing face-to-face intervention.

Young people will be excluded if they have active suicidal ideation and are seriously contemplating or planning a suicide attempt. Given that we do not know whether BlueIce will have any unintentional adverse consequences, it would not be safe to test it with a high-risk group who are actively suicidal. Second, young people will be excluded if they are diagnosed with psychosis or have a significant learning disability which might impede their ability to use the app. Third, we will exclude young people who have been subject to abuse within the last 6 months or are the subject of a safeguarding investigation. Finally, BlueIce is only available in English and we will therefore exclude those who are unable to understand English.

### Recruitment and Consent

Project information will be provided to all clinical teams and staff across Oxford Health. This will be followed by meetings with clinical teams and interested clinical staff to demonstrate BlueIce. Clinicians will be provided with project information sheets which they will be asked to discuss with eligible young people whom they think will benefit from BlueIce. The clinician will pass details of interested young people to the research team. The researcher will contact the young person to discuss the project and obtain written consent. For those under the age of 16, parental consent will also be required.

### Intervention

BlueIce is an Android smartphone app that has been coproduced with young people who have self-harmed. It contains a personalized toolbox of strategies that are available to the young person 24/7. It is designed to be used as an adjunct to therapy and includes a mood diary, a section of personalized mood-lifting techniques, and emergency contact numbers.

#### Mood Diary

Young people are able to monitor their mood each day. For each mood rating, they have the option of adding a note to record any particular reason why they might be feeling as they do. Their rating and notes are saved in a calendar which the young person and therapist can review to look for changes and patterns over time.

#### Mood Lifting

Young people who rate their mood as low will automatically be routed to the mood-lifting section of BlueIce. They can access this at any time directly from the main menu. This section contains a menu of mood-lifting activities personalized according to the interests of the young person. The activities are designed to counter the common reasons why young people self-harm (to punish themselves, emotional relief, feeling hopeless) and draws on common methods used in CBT and DBT. The mood-lifting section includes 8 activities:

Photographs, inspirational quotes, and pictures that are associated with happy memories can be uploaded and saved. These can be reviewed when low to help young people remember the positive things in their life.A music player is included where young people can upload and store music they enjoy and which has a positive effect on how they feel. This playlist can be readily accessed as a way of improving their mood.Young people can create a personalized list of physical activities they enjoy like going for a run or riding a bike or playing with siblings for review when they are low.Young people can create a list of activities—like making a cake, watching an episode of a favorite TV series, reading a book, playing with a pet—that can be reviewed when they are feeling down.Audio-recorded instructions for a 10-minute mindfulness session, calming visualization, and a quick controlled breathing exercise (4-7-8 breathing) are included. These can be used to help young people manage any unpleasant emotions or distressing thoughts.Young people can record any troubling thoughts that are racing through their heads into the thought diary. These can be directly typed into BlueIce where they are saved and can be reviewed with the clinician at a later date. This allows identification of any particular themes that could be addressed during face to face work with their clinician.This section draws on ideas from DBT and helps young people tolerate their distress. This includes instructions for an ice dive, a sensory toolbox, and a pros and cons balance sheet for self-harming.The final section contains the phone numbers of 3 to 5 people whom the young people could contact if they were feeling low and in danger of self-harming. These would be people who make them feel happy and those they could talk with about how they are feeling. This section prompts the young person to reach out to others.

